## Objectives

PrimaryPeritonitis-related complications (Table 1) within 30 or 90 days and one year after index surgerySecondaryCCI within 30 or 90 days and one year after index surgeryMortality within 30 or 90 days and after one yearSOFA score and C-reactive protein (CRP) measured in the first seven days after index laparotomyIncisional hernia rate after 12 months assessed by clinical examination and abdominal CT-scanQuality of life after 3 and 12 months assessed by the SF-36 questionnaireHospital care utility within three months after index surgery (Table 2)TertiaryThe concentration of lactate, glycerol, pyruvate, glucose, and cytokines in the peritoneal fluid in a subgroup of 10 patients from each group measured by intraperitoneal microdialysis on postoperative days 0–4

**Table 1 Tab1:** Peritonitis-related complications

Disease-related major morbidity needing readmission and conservative treatment but not surgery
Fistula: non-anatomical connection between intestine and cutis, communication between GI tract and external atmosphere or between 2 hollow organs
Wound dehiscence/incisional hernia with obstruction: full-thickness discontinuity in the abdominal wall with bulging of abdominal content
Abscess needing percutaneous drainage: pus-containing non-pre-existing cavity confirmed by positive Gram stain or culture
Renal failure: urine production < 500 mL/24 h with rising levels of blood urea nitrogen and creatinine combined with dehydration (decreased circulating volume with elevated haematocrit needing intravenous rehydration) based on inadequate oral intake, nausea/vomiting, or both (only when needing readmission)
Myocardial infarction (electrocardiogram and enzyme changes suggestive of myocardial infarction or needing admission to coronary care unit), pulmonary embolus (ventilation-perfusion mismatch on lung scintigraphy), or cerebrovascular accident (ischemic or non-ischemic with persistent paresis or paralysis without previous history)
Gastric or duodenal bleeding: needing endoscopic treatment or embolisation therapy
Respiratory failure due to pneumonia, pleural effusion, or pulmonary oedema and needing oxygen therapy or mechanical ventilation
Urosepsis: urinary tract infection with positive urine and blood cultures and circulatory shock

Disease-related major morbidity needing surgical intervention during first admission or readmission

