## Methods

### Study design

A multicentre non-blinded superiority randomised controlled trial on VAC vs. ROD. Danish, as well as other European centres, will be invited to participate. The study protocol adheres to the guidelines determined in Standard Protocol Items: Recommendations for Interventional Trials (SPIRIT) (Additional file 2) [45].

The VACOR study will include two separate studies: VACOR-Main and VACOR-Microdialysis.

All centres must participate in the VACOR-Main study, with only Odense University Hospital participating in the VACOR-Microdialysis study. VACOR-Main will report on all primary and secondary outcomes; in VACOR-Microdialysis, a sub-study of 10 patients from each group will be included. A microdialysis catheter will be placed in the peritoneal cavity, and samples of the peritoneal fluid will be collected every 6th hour to measure the concentration of lactate, glucose, pyruvate, glycerol, cytokines (IL-1b, IL-6, IL-10, TNF-a) and metalloproteins (MMP9 and MMP8). The purpose is to investigate intraperitoneal metabolic changes and inflammatory responses in the two groups.

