#### Microdialysis

The intraperitoneal microdialysis catheter will be placed before the abdominal closure or before applying the VAC system. The microdialysis catheter (M-dialysis 63, Microdialysis AB, Stockholm, Sweden) will be introduced through the abdominal wall outside the laparostoma via a charrier ten split cannula and placed in the peritoneal cavity between small intestine loops. The catheter will be perfused by an isotonic perfusion fluid (Perfusion fluid CNS Dextran, Microdialysis AB, Stockholm, Sweden) via a small pump (Microdialysis CMA 106 pump, Microdialysis AB, Stockholm, Sweden) at a flow rate of 0.3 μl/min. The catheter will be anchored to the skin. Samples will be collected in vials at 6-h intervals for the first four postoperative days. Bedside analysis for lactate, glycerol, and pyruvate concentration will be made via the ISCUSflex Microdialysis Analyzer (Microdialysis AB, Stockholm, Sweden). After analysis, the samples will be stored at  − 80 °C to analyse cytokine and MMP concentrations.

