The interim analysis will be performed at 25%, 50%, and 75% of recruited patients on the primary outcome after 30-days to detect significant differences between groups at the earliest possible time, ultimately leading to the termination of the study. We have adjusted our power calculation to the interim analyses using the O'Brien–Fleming method. The study group will have access to the results of the interim analyses and may make the final decision to terminate the study.

All of the above analyses will be performed as both intention-to-treat (patients will be analysed according to their randomisation group) and per-protocol analysis (what actually happened). The main analyses will be performed as complete case analyses. Multiple imputations will impute missing values in a supplementary analysis, including baseline characteristics as predictors.

*P* values < 0.05 will be considered statistically significant. Statistical calculations will be performed using Stata software (version 15, Stata Corp LP, Texas, USA).

In the VACOR-Microdialysis sub-study, the parameters will be compared using descriptive statistics for continuous and discrete variables. Repeated measurement across time points will be compared by mixed-effects regression models, including the interaction between time points and operation method and a random intercept for each patient. In addition, normality assumptions will be graphically assessed using quantile–quantile plots.

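### The microdialysis model names a random intercept but no serial correlation, which can inflate the joint time-by-operation test in 6-hourly samples

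*Protocol article*

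**What the plan says.** The last paragraph of Statistical analysis in the protocol article covers the VACOR-Microdialysis sub-study. After descriptive statistics, it plans a mixed model for the repeated samples and specifies it as "including the interaction between time points and operation method and a random intercept for each patient". The one model check it adds is a graphical check of normality by quantile–quantile plots.

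The rest of the design is given elsewhere in the article:

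- **Size** (Study design): "a sub-study of 10 patients from each group will be included", at one centre.
- **Sampling** (Microdialysis): "Samples will be collected in vials at 6-h intervals for the first four postoperative days", through one catheter per patient. Objectives words the period as "measured by intraperitoneal microdialysis on postoperative days 0–4" and ranks the outcome as tertiary.
- **Aim** (Study design): "The purpose is to investigate intraperitoneal metabolic changes and inflammatory responses in the two groups".
- **Significance rule** (Statistical analysis): "values < 0.05 will be considered statistically significant".

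The article gives no residual covariance structure, autocorrelation, coding of time (categorical or linear) or small-sample degrees of freedom for this model.

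**The concern.** With independent residuals, a random intercept gives every pair of samples from one patient the same correlation. That suits a few widely spaced visits. It suits less well a dense series from one fixed, continuously perfused catheter, where neighbouring values are likely to be more alike than distant ones. Events during follow-up add to this. Dressing changes about every 48 hours or as needed, and relaparotomies decided patient by patient, can shift several consecutive samples together at times that differ between patients. A constant patient effect cannot absorb such shifts.

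The time-by-operation interaction is judged against within-patient variation. If errors are positively autocorrelated, slow drifts within a patient vary more than the pooled residual mean square suggests, so the interaction test rejects a true null too often. A quantile–quantile plot does not reveal this, because autocorrelated residuals can be perfectly normal.

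The model would be applied to about ten analytes (four metabolites, four cytokines, two metalloproteins) in 20 patients. At stake is a chance finding reported as a biological difference between the two strategies. The Discussion says that no human randomised trial has compared bio-mediators between them.

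**Working it through.** **Inputs from the protocol article**

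- Patients: 10 per group, 20 in total (Study design).
- Samples per patient: 4 days × 24 h / 6 h = 16 (Microdialysis). If days 0–4 are counted as five full days, 5 × 24 / 6 = 20 (Objectives).
- First to last of 16 samples: 15 × 6 h = 90 h.
- Nominal level: 0.05 (Statistical analysis).

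**Assumptions not in the documents**

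- Errors follow AR(1), with correlation ρ between adjacent 6-hour samples, added to a patient intercept. ρ is varied from 0 to 0.9.
- A second scenario makes half of the within-patient variance independent noise.
- Data are complete and there is no true group difference.

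**What the stated model implies.** Under AR(1), the residual correlation k samples apart is ρ^k. At ρ = 0.7 it is 0.7 for neighbours and 0.7^15 ≈ 0.005 at 90 h. The random-intercept model treats both pairs alike.

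**Tests.** Let n = 10 per group and T = 16.

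- *Categorical time.* With balanced data the random-intercept interaction test is F = [SS_int/(T−1)] / [SS_within/((2n−2)(T−1))]. Here SS_int = (n/2) Σ(d_t − d̄)², and d_t is the group difference in means at time t. The degrees of freedom are 15 and 18 × 15 = 270.
- *Linear time.* z = (b_VAC − b_ROD) / √(s² · 2/(n·S)), with S = T(T²−1)/12 = 16 × 255/12 = 340 in squared sampling intervals, and s² the within-patient residual variance.

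**The plan's own figure first.** At ρ = 0 the stated model is true. The simulated type I error is 4.7% (categorical) and 5.2% (linear), so the nominal 5% is reproduced.

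**Type I error at nominal 5%, T = 16** (10,000–20,000 replicates; at 20,000 the simulation error near 10% is √(0.1 × 0.9/20,000) ≈ 0.2 points)

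| ρ | Categorical | Categorical, half noise | Linear | Linear, half noise |
|---|---|---|---|---|
| 0.3 | 6.3% | 5.4% | 13.6% | 9% |
| 0.5 | 8.8% | 5.6% | 22.8% | 14% |
| 0.7 | 11.3% | 6.3% | 33.5% | 20% |
| 0.9 | 14.3% | 6.5% | 46.9% | 24% |

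Separate runs at ρ = 0.9 put the categorical test between 14% and 16%. The half-noise categorical test peaks at 7.3%, at ρ = 0.8. With 20 samples the categorical test gives 10.1% at ρ = 0.6 and 16.0% at ρ = 0.9.

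**A separate small-sample effect.** A Wald chi-square test with maximum-likelihood variance gives 10.0% even at ρ = 0, and 19.1% at ρ = 0.9. The 10.0% comes from the small sample, not from serial correlation.

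**Comparisons that are not affected** (patient variance share 0.3, ρ from 0 to 0.9)

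- Group difference at one time point: 5.1% rising to 5.8%.
- Overall group effect: 4.9–5.3%.
- Group difference in change between adjacent samples: 4.7% falling below 1%, so conservative.

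**After the fix** (data generated as AR(1) plus random intercept)

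- REML with random intercept and AR(1) residual, F reference: 6.5% at ρ = 0.6 and 5.0% at ρ = 0.8. With a chi-square reference: 7.3% and 5.9%.
- Greenhouse–Geisser-corrected interaction test: 2.0–4.6% for ρ from 0.3 to 0.9.
- t-test on patient slopes: 5.0–5.1% at every ρ.

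**The case against.** The strongest reply is that this is one sentence in a condensed article. It lists what the model includes and does not say that the random intercept is its only dependence term. Residual covariance and degrees of freedom are often settled in a full protocol or analysis plan, and neither is shown. This stands as far as it goes: one cannot infer that serial correlation will be ignored, only that the model as written has no term for it. But the sentence does choose a dependence structure, and that structure fits this sampling scheme poorly. It can be improved whatever a later document adds.

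Second, a reader might infer that the test rejects two to three times too often as a matter of fact. The documents do not support that. They give no autocorrelation. For the categorical test, a doubling needs ρ of about 0.6 or more with no independent noise; with half noise the excess is slight. The large linear-time figures need a coding of time that the article does not state, and its reference to time points reads more naturally as categorical.

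Third, no joint interaction test is named. The same model could be used to estimate group differences at each time point, and those are close to nominal. It would therefore be wrong to say that the model's standard errors are invalid throughout. The problem lies in the joint test and in slope or long-span contrasts.

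Fourth, a family-wise figure is tempting. With ten analytes, 1 − 0.95^10 = 40%, rising to 61–82% if the per-test error reflects ρ of 0.5–0.9. That treats analytes from the same fluid and patients as independent, and the 40% is multiplicity alone. It should not be used as the size of this point.

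**Conclusion.** The point holds in a conditional form. As written, the model implies equal correlation between all of a patient's samples. If neighbouring samples are positively autocorrelated, the joint time-by-operation test is anti-conservative. For assumed AR(1) correlations of 0.3 to 0.9, its error at nominal 5% is about 6–16% with categorical time (about 5–7% with half independent noise) and about 13–47% with linear time (about 9–24% with that noise). The direction follows from the design. The size rests on assumptions about autocorrelation, noise and time coding that the documents cannot settle.

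A reader might extend this to the trial's main conclusions, but nothing supports that: the primary and secondary outcomes do not use this model. The point is confined to a tertiary, exploratory sub-study of 20 patients at one centre, and it is minor.

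**What to change.** Add one sentence to the sub-study paragraph: the mixed model keeps the random intercept per patient, adds a serially correlated residual (AR(1) for equally spaced vials, or exponential in time if vials are missed), and is fitted by REML with a small-sample degrees-of-freedom correction. The same sentence should say whether time is categorical or linear, and whether the interaction is tested jointly. The degrees-of-freedom correction also deals with the separate small-sample inflation of the chi-square test.

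If the AR(1) fit proves unstable with 20 patients, a Greenhouse–Geisser-corrected interaction test or a t-test on patient slopes is a simple fallback. The first is somewhat conservative; the second looks only at linear change.

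The cost is one model option, which the named software can fit, and slightly less favourable p-values. Data collection, sample size and trial conduct do not change.

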#### Dissemination policy

The study results will be published in scientific international peer-review journals and presented at relevant conferences. Results will be available to participants, healthcare professionals, the public, and other relevant groups in an anonymous patient format. The study protocol will be publicly accessible. Authorship eligibility adheres to Vancouver conventions guidelines.

## Discussion

The VACOR trial addresses several important unanswered clinical questions in the surgical treatment of complicated intra-abdominal infections with special reference to the choice of primary abdominal closure with ROD or the open abdomen with VAC treatment.

In some conditions such as severely complicated peritonitis, second look for ischemia and septic shock, where patients have substantial visceral oedema with high risks of abdominal compartment syndrome, establishing an OA with VAC may be preferred [5, 17, 19, 24]. According to intention-to-treat and per-protocol principles, these patients will be included in the present study. The OA with VAC treatment may have several benefits, including drainage of residual infection, preventing intra-abdominal compartment syndrome, and the timely treatment of complications. The disadvantages are incisional hernia and EAF [23, 42, 44, 51–55]. A recent review of temporary abdominal closure techniques found a higher incidence of EAF in septic than non-septic patients (12.1% vs. 3.7%, respectively) [56]. A large cohort study by Coccolini et al. [57], including 649 patients treated with OA where most patients had peritonitis, could not confirm that peritonitis or temporary abdominal closure with or without negative pressure was related to the incidence of EAF. In systematic reviews with meta-analyses and non-randomised studies it has been shown that VAC is the safest of all temporary abdominal closure techniques [21, 31–43].

In a study including patients with severe secondary peritonitis, patients were randomised to OA with non-resorbable polypropylene mesh versus primary closure with ROD [58]. The study was discontinued at the first interim analysis. The study showed an insignificant higher mortality risk in the OA group of 55% compared to 30% in the ROD group. However, there was a relative risk of 1.83 and an odds ratio of 2.85 in the OA group. Hence, the authors concluded a tendency towards a better outcome in the ROD group.

Animal and in silico studies suggest that VAC treatment suppresses systemic inflammatory reactions and prevents multi-organ failure by draining the peritoneal fluid [59, 60]. In a small animal study comparing VAC to passive drainage after inducing abdominal sepsis, the mortality rate was 17% versus 50%. This difference was not statistically significant (*p* = 0.19), likely due to the small number of included animals [60]. In the only human RCT, levels of plasma and peritoneal cytokines in patients with abdominal trauma and intra-abdominal sepsis were compared [61]. Participants were allocated to Barker's or vacuum pack. The study revealed no significant difference in bio-mediator levels or peritoneal drainage. However, a significant difference was observed in 90-day mortality (21.7% vs. 50%), favouring the VAC group. No human RCT studies compare bio-mediators in VAC versus primary closure with ROD.

Diagnosing postoperative or ongoing abdominal complications with the ROD strategy can sometimes be challenging. The literature suggests that progressive or persistent organ failure in the early postoperative phase is the best indicator of positive findings and ongoing infection [20, 26, 62]. The choice of whether or not to perform a relaparotomy is often subjective, based on local guidelines and personal experiences [25–28]. In a randomised study 112 patients with secondary peritonitis were included in the ROD arm and 113 in the planned relaparotomy arm [20]. A total of 42% of patients in the ROD group received relaparotomies, 71% had negative findings, and 29% had positive findings at the relaparotomy, respectively.

As well as our study, another randomised multicentre trial, the COOL study [63], is actively recruiting patients with secondary peritonitis to either VAC or primary closure. The primary endpoint is the 90-day mortality rate. The COOL study includes severely ill patients, assessed by physiological scores and secondary peritonitis originating from the lower- and upper gastrointestinal tract, gallbladder, and adnexa. The current study includes patients with secondary peritonitis from the lower gastrointestinal tract with purulent, enteric, or faecal contamination in a minimum of two out of four abdominal quadrants, irrespective of the patient's general condition. Therefore, there is a risk that some patients may be overtreated. However, the risk might be low since we have excluded patients with upper GI perforations, appendicitis, pancreatitis, and local peritonitis. The majority of the patients are expected to be septic, and the literature has indicated that these patients may benefit from VAC treatment [17, 19, 24]. There might be a grey zone of precisely which patients may benefit from VAC treatment. The COOL trial includes only cases where the surgeon a priori finds that VAC might be beneficial before the randomisation takes place. Our study explores the generalisability of VAC or abdominal closure as the main principle in patients with diffuse peritonitis from the lower gastrointestinal tract. Our study and the COOL study utilise inclusion via a surgical equipoise, ensuring that a high fraction of eligible patients will be included.

A limitation of the current study is that the power calculation is based on peritonitis-related complications and not the CCI-index due to the literature lacking explicit results for VAC and ROD. The abdominal condition at index operation will be classified according to Bjorck's amended classification [48]. The system was intended for established open abdomens rather than the abdominal condition at the index operation. Nonetheless, it is a novel usage for this reviewer. However, this might be another valuable aspect of our study to comment upon whether the classification is further helpful for general use in acute general surgery.

## Conclusions

There is no robust evidence for choosing either open abdomen with VAC treatment or primary closure with relaparotomy on-demand in patients with secondary peritonitis. The present study has the potential to answer this important clinical question.

## Data Availability

On request, data can be shared in an anonymised form if a data processor agreement is obtained.

## Abbreviations

VAC: Vacuum-assisted closure
PR: Planned relaparotomy
ROD: Relaparotomy “on-demand”
CCI: Comprehensive complication index
SF-36: Short form survey 36
OA: Open abdomen
EAF: Enteroatmospheric fistula
CT: Computed tomography
CRP: C-reactive protein
CI: Confidence interval
OPEN: Odense Patient data Explorative Network
ASA: American Society of Anesthesiology
APACHE II: Acute Physiology and Chronic Health Evaluation II
SOFA: Sequential Organ Failure Assessment
ICU: Intensive care unit
DRG: Diagnosis-related groups
